## Discussion

Since the publication of the 2010 IOM report on vitamin D and the design of the MDIG trial and dosing regimens in 2012, there have been several new reports of biochemical and clinical findings of prenatal vitamin D supplementation trials conducted in Iran [67–69], the United Arab Emirates [70], Pakistan [71], New Zealand [72], and Australia [73]. However, in none of these studies did researchers report postnatal infant growth outcomes, and all trials enrolled fewer than 100 participants per arm, suggesting they lacked power to detect effects on most pregnancy-related and infant clinical outcomes. The results of a relatively larger trial (*N* = 549) recently completed in rural Pakistan (NCT01229189) have not yet been released publicly. There are at least three other large trials underway: the Maternal Vitamin D Osteoporosis Study, for which the primary outcome is neonatal whole body bone mineral content [74]; the Vitamin D Antenatal Asthma Reduction Trial [75]; and the Vitamin D Supplementation during Pregnancy for Prevention of Asthma in Childhood (ABCvitaminD trial; ClinicalTrials.gov identifier NCT00856947). However, these and other registered prenatal vitamin D trials are being conducted in high-income countries.

The MDIG trial will therefore offer unique insights into the effect of improving maternal-infant vitamin D status in a low-income setting where vitamin D insufficiency is common and there is a high prevalence of infant linear growth faltering. The trial is primarily designed and powered to evaluate the dose–response effects of vitamin D on infant length, an outcome that is directly aligned with the classical role of vitamin D in mineral metabolism and bone health but may also be interpreted as a surrogate marker for organ (including brain) growth and development. Serial specimen collection and frequent clinical follow-up will enable a range of secondary objectives to be addressed, including tests of mechanistic hypotheses (e.g., mediation of the beneficial vitamin D supplement effect on skeletal length by PTH suppression) and assessments of the effects of the intervention on infant morbidity (in particular, the incidence of acute respiratory infections in the first 6 months after birth). Longer-term surveillance of the infant cohort will ideally enable the assessment of other important clinical outcomes (e.g., asthma, neurodevelopment) that may be influenced by the non-classical role of vitamin D in immunoregulation and extraskeletal cellular proliferation and differentiation.

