Observational studies of the association between maternal prenatal vitamin D status and infant anthropometry have yielded conflicting findings [19–23]. The effects of prenatal vitamin D supplementation on infant length have not been widely studied in controlled trials. In a study conducted in the 1970s in London, England, prenatal vitamin D supplementation reduced the risk of small for gestational age (SGA) versus control, but there was no significant effect on birth length [24]; however, the infants in the vitamin D group had significantly greater mean length at 1 year of age [25]. We recently completed a randomized, placebo-controlled, double-blinded trial of maternal third-trimester vitamin D_3_ supplementation in Dhaka, in which 160 women were randomized to receive either 35,000 IU/wk or placebo until delivery. Maternal mean 25(OH)D was significantly higher at delivery after receiving vitamin D versus placebo (134 vs. 39 nmol/L; *P* < 0.001; *N* = 133). There was a parallel difference in cord 25(OH)D (103 nmol/L in vitamin D group vs. 39 nmol/L in placebo group; *P* < 0.001; *N* = 132) [16]. Analyses of the effect of prenatal vitamin D supplementation on infant length among 134 infants followed up to 1 year of age revealed that infants born to women in the vitamin D group had mean length for age z-scores (LAZs) at 1 year that were significantly greater than infants in the placebo group (mean = 0.44 z-score units higher; 95% confidence interval [CI], 0.06–0.82) [26]. This corresponded to an approximate halving of the prevalence of stunting (11 % vs. 21 %), which would constitute a substantial public health benefit. The effect appeared to be attributable to a significantly accelerated increase in mean LAZ from birth to 1 month of age (change of 0.53 z-score in vitamin D versus 0.19 z-score in placebo group; *P* = 0.004) rather than a significant difference in birth length [26]. However, some animal [27] and observational [21, 28] studies have suggested an effect of maternal prenatal vitamin D status on growth of the fetus.

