### Design and sample size

The MDIG trial is a randomized, placebo-controlled, double-blinded, dose-ranging trial with a 1:1 allocation ratio across five parallel groups (Fig. 1). A total of 1300 pregnant women will be randomized, with a target of allocating 260 women in each group (Fig. 1). The primary outcome analysis will be a between-group comparison of mean LAZs at 1 year of age, assuming up to 15 % attrition from each group before this time point. To assess the effect of prenatal vitamin D, we plan to perform five primary between-group analyses, comprising each vitamin D dose versus placebo (three comparisons) and comparisons between adjacent doses (two comparisons). A conservative approach to addressing multiple testing is to partition the α (risk of type I error) among the five comparisons (conventional overall 0.05 divided by 5); thus, each between-group comparison will be tested as a two-sided test with an α of 0.01, assuming 90 % power. With 220 analyzable participants per group (about 85 % of total enrolled), the minimum detectable difference in LAZ will be 0.40 z-score units, which equates to approximately 1.0 cm at 1 year of age based on WHO growth standards. In our preliminary trial, we observed an increase in LAZ of 0.44 at 1 year attributable to prenatal vitamin D supplementation, which corresponded to an increase of 1.1 cm (95 % CI, 0.06–2.0), adjusted for sex [26].

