### Interventions and control

#### Vitamin D doses

The primary objective of the MDIG trial is to establish evidence of a causal relationship between maternal-infant vitamin D status and infant stature. A randomized dose-ranging trial enables robust causal inferences based on dose–response effects, in addition to relatively unbiased comparisons with the placebo group. Three vitamin D_3_ doses (4200 IU/wk, 16,800 IU/wk, and 28,000 IU/wk) were selected on the basis of preliminary data, published literature, and consideration of the 2010 IOM dietary reference intakes [38] (see Additional file 1 for detailed rationale). Pharmacological principles and empirical data indicate that weekly doses of vitamin D achieve 25(OH)D levels similar to equivalent daily doses [39]; thus, the equivalent daily doses in increasing order are 600 IU/day, 2400 IU/day, and 4000 IU/day. Our previous pharmacokinetic findings among pregnant women in Dhaka [16, 40] have generally been consistent with published estimates of the vitamin D-to-25(OH)D dose–response relationship in non-pregnant adults (i.e., an approximately 0.7 nmol/L increase in 25(OH)D at steady state for each 1 μg/day of vitamin D_3_ [41, 42]). The preliminary pharmacokinetic studies have provided evidence of the biochemical efficacy, tolerability, and short-term safety of doses of up to 35,000 IU/wk in pregnancy in the target population. Hollis et al. previously reported that doses up to 4000 IU/day were well tolerated and efficacious at raising 25(OH)D in pregnant women in the United States [43].

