### Statistical analysis

For the primary trial efficacy outcome analysis, mean LAZ (at 1 year of age) will be compared across groups using analysis of variance. To assess the effect of prenatal vitamin D on mean LAZ at 1 year of age, we plan to perform five primary between-group analyses: each prenatal vitamin D dose versus placebo (three pairwise comparisons), as well as comparisons between all adjacent vitamin D doses (two pairwise comparisons). Because the primary hypotheses relate to differences between two groups, each analysis will be akin to an independent-samples *t* test. The primary effect measure for each comparison will be expressed as a mean difference between groups with 95 % CI. However, an overall α for statistical significance for all five comparisons will be 0.05 (two-sided), and the Holm test will be used to account for multiple testing. Therefore, even if the 95 % CI for a particular mean difference does not include zero, it is possible that it may not be considered statistically significant when all five comparisons are presented together. The postpartum effect analysis will be the comparison of mean LAZ at 1 year of age between infants of mothers who received 28,000 IU/wk versus placebo in the postpartum period (among women who received 28,000 IU/wk prenatally), using a statistical approach similar to that described for the prenatal effect analysis. The nominal αfor statistical significance will be 0.05 (two-sided test) for this analysis. Because there is only one primary pairwise comparison related to the postpartum effect, no adjustment for the multiplicity of outcomes is planned.

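### The Discussion claims power for dose–response, but the sample size covers only pairwise differences of 0.40 LAZ, and no trend contrast or regression on dose is planned in the text shown

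*Protocol article*

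**What the plan says.** The Discussion of the protocol article states: "The trial is primarily designed and powered to evaluate the dose–response effects of vitamin D on infant length". The section on vitamin D doses gives the reason for several doses: "A randomized dose-ranging trial enables robust causal inferences based on dose–response effects". The same sentence also names comparison with placebo as a second basis for inference.

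Under Design and sample size, the prenatal analyses are "each vitamin D dose versus placebo (three comparisons) and comparisons between adjacent doses (two comparisons"). For the sample size, "each between-group comparison will be tested as a two-sided test with an α of 0.01, assuming 90 % power". With 220 analyzable infants per group, the minimum detectable difference is given as 0.40 LAZ. The Statistical analysis section repeats the same five comparisons under an ANOVA framework, each resembling a two-sample t test, and adds that "the Holm test will be used to account for multiple testing" at an overall 0.05.

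The text contains no trend test, dose contrast or regression on dose. The regression splines in the Statistical analysis section are over time. The only effect size cited is 0.44 LAZ, from a preliminary trial in which "160 women were randomized to receive either 35,000 IU/wk or placebo until delivery". No expected difference between adjacent doses is given.

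**The concern.** The article says what the trial is powered for, but the calculation behind it concerns something else: whether two given arms differ by 0.40. A dose–response question asks whether length rises with dose over all arms, and a graded rise splits the total effect into smaller steps. The adjacent-dose tests then face differences well below 0.40.

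The risk lies in interpretation. A real graded effect could leave the top dose significantly better than placebo and neither adjacent comparison significant. Readers told that the trial was powered for dose–response could take this as evidence that no dose–response exists.

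**Working it through.** **Inputs.** From Design and sample size: n = 220 per group; two-sided α = 0.05/5 = 0.01 for each prenatal comparison; 90% power; 0.40 LAZ detectable prenatally; 0.31 LAZ detectable postpartum at two-sided 0.05. From Background: 0.44 LAZ at 35,000 IU/wk. The SD of LAZ is not stated.

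**The plan's own figures.** Minimum detectable difference = SD × √(2/n) × (z₁₋α/₂ + z₀.₉₀), with √(2/220) = 0.0953.
- Postpartum, SD 1.00: 0.0953 × (1.960 + 1.282) = 0.309. This matches the stated 0.31.
- Prenatal, SD 1.00: 0.0953 × (2.576 + 1.282) = 0.368, not 0.40. The stated 0.40 needs SD = 0.40/(0.0953 × 3.857) = 1.09.

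The two figures therefore imply SDs of 1.00 and 1.09, and both are carried through below. At SD 1.09 the statement of 90% power at 0.40 is arithmetically sound for any pair.

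**A bound that needs no curve.** Suppose the response never falls with dose and totals at most 0.44 at 28,000 IU/wk. The steps 4200→16,800 and 16,800→28,000 then sum to at most 0.44, so at least one is at most 0.22. Power ≈ Φ(δ/(SD × 0.0953) − z₁₋α/₂).
- SD 1.00: Φ(2.307 − 2.576) = 39%.
- SD 1.09: Φ(2.121 − 2.576) = 32%.

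Holm can relax the threshold, but never beyond 0.05. Even there the ceiling is Φ(2.307 − 1.960) = 64% or Φ(2.121 − 1.960) = 56%. Both adjacent comparisons could face 0.40 only if the total were at least 0.80.

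**A linear response.** Two cases: 0.40 at 28,000 IU/wk, and 0.44 at 35,000 scaled down, 0.44 × 28/35 = 0.352. Adjacent differences are the total × 12.6/28 and × 11.2/28: 0.18 and 0.16 in the first case, 0.158 and 0.141 in the second. Holm results come from simulating the five tests on arm means (200,000 runs).

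| Total at 28,000 | SD | Adjacent power, α = 0.01 | Adjacent power, Holm | Top dose beats placebo, neither adjacent significant |
|---|---|---|---|---|
| 0.40 | 1.00 | 25%, 19% | 30%, 23% | 47% |
| 0.40 | 1.09 | 20%, 15% | 24%, 18% | 52% |
| 0.352 | 1.00 | 18%, 14% | 22%, 16% | 53% |
| 0.352 | 1.09 | 15%, 11% | 18%, 13% | 53% |

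Both adjacent comparisons reject in about 1–3% of runs.

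**One contrast on dose.** Use the four arms with placebo postpartum, with dose in thousands of IU/wk: 0, 4.2, 16.8, 28, mean 12.25. Coefficients c = −12.25, −8.05, 4.55, 15.75; Σc² = 483.63. SE = SD × √(483.63/220) = 1.483 × SD. Under linearity the contrast equals slope × Σc².
- Total 0.40: (0.40/28) × 483.63 = 6.909. Dividing by the SE gives 4.66 (SD 1.00) or 4.28 (SD 1.09); power at two-sided 0.05 is 99.7% or 99%.
- Total 0.352: (0.352/28) × 483.63 = 6.080. Dividing by the SE gives 4.10 or 3.77; power is 98% or 96%.

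**The case against.** Several stronger readings are tempting, and the article does not support them.

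- A reader might infer that the primary analysis misses the primary aim. It does not. The Objectives frame the prenatal aim as each dose against placebo, and three of the five comparisons address exactly that.
- A reader might infer that dose–response is ignored. Adjacent-dose comparisons are defined by dose order and ask whether more dose adds effect. What is absent is a test that uses all arms together. A statistical analysis plan not shown could add one as supportive, but the primary family and its power are fixed here without it.
- A reader might infer that the plan needs every step to be 0.40, and so a total of 1.2 LAZ. The 0.40 is a conditional detectable difference: if a pair differs by that much, power is 90%. The article does not say that all steps are that large.
- A reader might infer that adjacent tests always have low power. This depends on shape. If the whole 0.40 falls between 4200 and 16,800 IU/wk, that comparison has 92–96% power under Holm. The preliminary trial also began supplementation in the third trimester, so its effect need not carry over to this trial.
- A reader might infer a heavy α cost to the placebo comparisons. Dividing by 3 instead of 5 raises power at 0.40 only from 90% to 93% (SD 1.09), and the 0.01 shares serve sizing, since analysis uses Holm.

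Making a trend test the gatekeeper would also be a trade-off, not a correction. With a plateau of 0.40 from 4200 IU/wk, the chance of declaring any dose superior to placebo would fall from 98–99.5% to 86–91%. Finally, mean differences with 95% CIs will be reported for every comparison, so a graded pattern would be visible to a careful reader.

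All of this stands. It narrows the point to the power claim and the missing contrast on dose, and it does not answer those two.

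**Conclusion.** The concern holds in a limited form. The claim of power for dose–response goes beyond the calculation that supports it, and the text shown contains no analysis that tests the dose trend directly. The primary pairwise family and its 0.40 detectable difference need not change on this account.

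The bound on the weaker adjacent comparison assumes only monotonicity, a total of at most 0.44, 220 infants per arm and an SD between 1.00 and 1.09. The Holm figures, the figure of about one trial in two, and the 96–99.7% for the contrast also assume a linear response reaching 0.35–0.40 at 28,000 IU/wk. The contrast is less favourable for an early plateau: if the whole 0.40 is reached at 4200 IU/wk, its power is 86–91%.

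**What to change.** Before unmasking:

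1. Pre-specify one single-degree-of-freedom contrast on dose (0, 4200, 16,800 and 28,000 IU/wk; the four arms with placebo postpartum), two-sided 0.05, as a key supportive dose–response analysis. Keep it outside the Holm family and do not make the dose-versus-placebo tests depend on it.
2. Reword the Discussion so that the power claim covers pairwise differences of 0.40 LAZ only.
3. State that the two adjacent-dose comparisons are not expected to have 90% power under a graded response of the preliminary trial's size, so a non-significant adjacent result is not evidence against dose–response.
4. State the SD assumed for LAZ, since 0.40 and 0.31 imply different values.

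The cost is one extra pre-specified analysis, less sensitive to early-plateau or non-monotone shapes, and a less favourable power statement. Sample size, data collection and the existing primary tests are unaffected.

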## Trial status

As of July 2015, enrollment is ongoing.

## Abbreviations

ARI: acute respiratory infection
Ca:Cr: calcium-creatinine ratio
CI: confidence interval
DSMB: Data and Safety Monitoring Board
EDTA: ethylenediaminetetraacetic acid
ERC: Ethical Review Committee
FGF: fibroblast growth factor
GA: gestational age
Hb: hemoglobin
HC: head circumference
HCAZ: head circumference for age z-score
ICDDR: International Centre for Diarrhoeal Disease Research
IGF: insulin-like growth factor
IGFBP: insulin-like growth factor-binding protein
IL: interleukin
IOM: Institute of Medicine
ITT: intention to treat
25(OH)D: 25-hydroxyvitamin D
RKL: rump-to-knee length
LAZ: length for age z-score
LMP: last menstrual period
MCHTI: Maternal and Child Health Training Institute
MDIG: Maternal Vitamin D for Infant Growth
MUAC: mid-upper arm circumference
POC: point of care
PTH: parathyroid hormone
PTHrP: parathyroid hormone–related protein
SGA: small for gestational age
TIPT: Toronto Institute of Pharmaceutical Technology
TNF: tumor necrosis factor
TSC: trial steering committee
UAL: upper arm length
WAZ: Weight for age z-score
WFLZ: weight for length z-score
WHO: World Health Organization
WHO-GS: World Health Organization growth standards
